The anamnesis documents in each of the three clinics will be analyzed at the three measurement time points (t0; t1; t2). In t0, only the physician-filled medical history will be considered, while in t1 and t2, the now via the PPs DAC tool patient-filled medical history will be examined. In each clinic and at each time point, an intentional sampling approach [22] will analyze approximately *n* = 30 documents of patients treated in the respective clinics during the survey periods. This approach results in a total of *N* = 270 documents to be analyzed. These will be examined using document analysis according to Prior [24], allowing statements about changes in the quality and content of the anamnesis documentation [4]. Haas [13] describes three functional levels of clinical documentation. In its primary function, documentation supports the preparation and monitoring of the actual treatment process. In its secondary function, documentation can also serve as a basis for billing purposes or legal obligations. In its tertiary function, documentation is used to answer scientific questions in the field of biomedicine or health services research [13]. Depending on which of the three functional levels is considered, different criteria are suitable for making statements about the quality of the documentation. For documentation in patient records, the U.S. Institute of Medicine identified completeness, readability, accuracy, and informativeness as the most important criteria for high-quality documentation [9]. Weiskopf & Weng [30] also highlighted completeness as the most important criterion for the quality of documentation in electronic patient records, especially regarding the described secondary and tertiary functions of documentation. Wurster et al. [32] further confirmed completeness as the most commonly used criterion for operationalizing documentation quality when investigating the transition from paper-based to electronic documentation and as actually receptive to change through the implementation of digital innovations [31]. In a first step, the contents of the documentation are recorded. This involves examining whether there is a change regarding the intended information to be documented (e.g., food intolerances, vaccination status) and how this information can be documented (e.g., checkboxes, free text). Based on this, an exploratory approach will be used to determine whether and how the quality of those documents can be reflected through the completeness of relevant information (as dimension of data quality). Completeness is operationalized as a percentage indicating, for each time period and clinic, whether specific information is filled in (documented vs. not documented) across all records [32]. The analysis in the pre-post-post comparison allows statements about how physician-filled and patient-filled medical histories differ and whether the expected changes over time, according to Rogers [25], are evident.

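### Analysis D sets physician-filled histories before go-live against DAC users' histories after it, so completeness differences mix the DAC package with time, user selection and record selection

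*Protocol article*

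**What the plan says.** All of this stands in the Protocol article, Methods / design, part D (analysis of actual portal usage).

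- **Source of documents.** "In t0, only the physician-filled medical history will be considered, while in t1 and t2" is followed by "the now via the PPs DAC tool patient-filled medical history will be examined". No other source is named for t1 and t2.
- **Selection.** The records are chosen by "an intentional sampling approach", about 30 per clinic and time point. "This approach results in a total of *N* = 270 documents to be analyzed".
- **Measure.** "Completeness is operationalized as a percentage indicating, for each time period and clinic, whether specific information is filled in", counted across all records.
- **Inference.** The pre-post-post comparison "allows statements about how physician-filled and patient-filled medical histories differ and whether the expected changes over time" predicted by the diffusion theory are evident.

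Table 1 labels D as exploratory. Question D1 asks how history documentation changes over time as DAC is used.

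**The concern.** The closing sentence draws two conclusions from one set of percentages: how physician-filled and patient-filled histories differ, and whether documentation changes over time. Between t0 and the later waves, however, the period, the tool, the author, the patients who can contribute a document and the records picked may all change together. A higher percentage at t1 could arise because DAC collects more, because patients who choose DAC have better documented histories anyway, because something else changed in the clinic, or because of which records were picked.

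The Conclusion section says the results should support other hospitals and guide software developers. If a selection artefact were reported as a documentation gain, or as a loss, it would mislead both.

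**Working it through.** **1. The plan's own figure.** 30 documents × 3 clinics × 3 time points = 270. This reproduces.

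**2. What differs in each contrast.**

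| | t0 vs t1/t2 | t1 vs t2 |
|---|---|---|
| Calendar time | differs | differs |
| Tool and author (the DAC package) | differs | same |
| Patients who can contribute | any treated patient vs DAC users | DAC users, mix may shift |
| Record selection | intentional in each wave | intentional in each wave |

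**3. Whether user selection is real in this study.** The documents themselves say so.
- Part C plans interviews at t1 and t2 with patients who did not use DAC, so use is not universal after go-live.
- The Theory section expects people with high digital literacy to adopt early.
- Table 1, A4 and A5, expect use to differ by care setting and by how often a patient is treated.
- Table 1, A1–A3, expect the share of users with low literacy or low technology acceptance to rise during observation.

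**4. Possible size for t0 vs t1/t2.** The documents give neither uptake nor completeness, so every input here is an assumption. Let u be the share of patients who would use DAC, and let c_user and c_non be the completeness for user-type and non-user-type patients, unchanged by DAC or time. Suppose the t0 records represent all treated patients.

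- t0: u × c_user + (1 − u) × c_non
- t1/t2 (users only): c_user
- Apparent change = (1 − u) × (c_user − c_non)

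| Assumed gap | u = 10% | u = 30% | u = 50% | u = 70% |
|---|---|---|---|---|
| 10 points (80% vs 70%) | 9 | 7 | 5 | 3 |
| 20 points (85% vs 65%) | 18 | 14 | 10 | 6 |

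For example, 0.9 × 20 = 18. These are percentage points of apparent change with no true effect. If non-users had the better documented histories, the sign would reverse. Intentional picking could add to the figure or offset it.

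**5. t1 vs t2.** Let s1 and s2 be the shares of low-literacy users at t1 and t2, and g the completeness of high-literacy users minus that of low-literacy users. With no real change in documentation, the percentage moves by (s1 − s2) × g. If A1 holds, s2 exceeds s1 and the move is not zero unless g is zero.

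**6. A concurrent contrast.** Comparing DAC with physician-filled records within one wave removes calendar time but carries the whole gap c_user − c_non (10 or 20 points under the same assumptions). It is a useful second view, but it is not free of selection.

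**The case against.** The strongest reply is that D is exploratory and descriptive. Part D names no test and no effect estimate, it says that histories differ and not that DAC caused the difference, and D1 makes DAC documents the natural object of study. A changing user mix is also partly what the diffusion theory is about. This stands and lowers the severity. It does not rescue a sentence that offers both an author comparison and a time trend without any reservation about who the users are.

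Several stronger readings are tempting, and the documents do not support them.

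- **Author and DAC should be separated.** Under DAC the patient enters the history, so tool and author are one package. A contrast of DAC as delivered is legitimate.
- **All of these factors confound every comparison.** Between t1 and t2 the author and tool are constant.
- **The form is expected to change, so the denominator of completeness changes.** The plan only examines whether the requested items change, and completeness is counted per item across records. What remains is that percentages are comparable only for items requested on both forms.
- **Percentages from purposive picks mean nothing.** They describe the records picked. They do not represent a defined patient population.
- **The plan restricts t1/t2 to DAC users in so many words.** This is inferred: the restricting word in the text belongs to t0. No other later source is named, however.
- **Small cells prove the point.** At 30 records and 50% completeness the 95% half-width is 1.96 × √(0.5 × 0.5 / 30) = 17.9 points. That formula presupposes random sampling and would apply equally to a better design, so it does not measure this defect.
- **Sampling all patients at random would cure it.** At an assumed uptake of 10–20%, 30 records would hold only 3 to 6 DAC documents, and user selection would still affect the comparison by mode.

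**Conclusion.** The concern holds in this limited form. The t0 versus t1/t2 difference in completeness cannot be assigned to the DAC package, calendar time, user selection or record selection, and the t1 versus t2 difference cannot be split between time and a shifting user mix. The closing sentence of part D therefore claims more than the design supports.

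The size of the bias cannot be derived from the documents. The 3 to 18 points above rest wholly on assumed uptake and completeness gaps and only show that the effect need not be negligible. The conclusion also rests on reading DAC histories as the only source at t1/t2. Since D is exploratory, severity is low to moderate.

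**What to change.** Keep the 270 documents and change how those used for the percentages are chosen and reported.

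1. For completeness, select records at random or consecutively within each clinic and wave. Keep purposive picks for the content description.
2. At t1 and t2, stratify by mode, so that DAC records and some physician-filled records of non-users from the same weeks are both sampled. This assumes that such records exist for non-users.
3. Record the mode for each document.
4. Compare completeness only on items requested on both the t0 form and the DAC form.
5. Report by wave and, within t1 and t2, DAC against physician-filled. Any figure that pools the two strata should be weighted by the share of DAC use in that clinic and window; otherwise the sampling split sets it.
6. State that user selection remains both in the contrast of t0 with DAC records and in the contrast by mode, and limit the closing sentence to a descriptive comparison.

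The cost is a new selection rule, one more field on the extraction sheet and some rewording. The real price is fewer DAC documents per cell, since each physician-filled record at t1/t2 takes the place of a DAC record. If that is unacceptable, narrowing the closing sentence is the minimum change.

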To achieve the potential improvements, offering a PP alone is not sufficient. The given example of the obligation for statutory health insurers to offer their patients a voluntary electronic health record illustrates this. These electronic health records must be actively requested by each individual patient in order to be set up (opt-in). In 2019, before the law came into force, 62% of the patients with statutory health insurance declared their willingness to use the electronic health record [6]. However, only 0.5% had actually requested it by the end of 2021 [28]. The aim of the project presented is to prevent the example described above, for the PPs still to be implemented, that a politically enforced digital innovation is not utilized. It is therefore important to understand which factors influence the adoption of the PP and which barriers are experienced, in order to actively empower and support disadvantaged groups of people to use the PP.

The framing use case for the research project is the PPs tool of digital anamnesis collection (DAC). DAC refers to the approach of postponing the medical history taking before the actual appointment. With the help of the PP, the patients can use their computer or smartphone to enter their medical history, allergies, etc. at home at their own pace or with their relatives’ support. This is meant to improve the quality of the information, which is also available for the physician when planning the appointment and therefore allows the consultation to be more efficient and target-oriented [27]. On the other hand, the DAC is characterized by the fact that it must be equally used by both, patients but also the physicians in order to realize its potential to improve healthcare delivery, making it even more important to understand the described factors, influencing the adoption of the PP. Of particular relevance is the fact that all German hospitals will be required to offer such DAC in the future.

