
E)Analysis of changes in internal administrative and clinical parameters

In light of the fact that it is unclear to what extent the DOI can be applied to PP, it is unclear to what extent the hospital data collected for administrative purposes is suitable for making statements regarding potential improvements in care. To identify outcomes relevant for future research projects, an exploratory analytical approach is applied to the hospital data collected for administrative purposes from one participating clinic. If the utilization of PP leads to improvements in clinical outcomes, these improvements would be reflected in the administrative and clinical management data. For instance, parameters mentioned by Dumitrascu [10] such as the 30-day readmission rate, inpatient mortality, or 30-day mortality are analyzed. The data consist of administrative data for all outpatient and inpatient patients within a month at the three measurement points (t0; t1; t2). Data analysis involves descriptive and inferential statistics to compare the means of the examined parameters regarding potential differences at the three measurement points. The results provide initial indications of whether the parameters investigated here are suitable for assessing potential impacts of the PP on clinical outcomes in further research projects.

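### Part E: an effect of portal use reaches clinic-wide means only in proportion to uptake, so an unchanged mean cannot show that a parameter is unsuitable

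*Protocol article*

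**What the plan says.** All of this stands in Methods / design, part E (internal administrative and clinical parameters), unless noted.

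- Status and setting: an "exploratory analytical approach is applied to the hospital data collected for administrative purposes from one participating clinic".
- Population: "The data consist of administrative data for all outpatient and inpatient patients within a month at the three measurement points (t0; t1; t2". There is no restriction to portal users.
- Parameters: outcomes "such as the 30-day readmission rate, inpatient mortality, or 30-day mortality are analyzed". No base rates are given.
- Analysis: to "compare the means of the examined parameters regarding potential differences at the three measurement points".
- Premise: "If the utilization of PP leads to improvements in clinical outcomes, these improvements would be reflected in the administrative and clinical management data". No condition on uptake is attached.
- Use of the result: "The results provide initial indications of whether the parameters investigated here are suitable for assessing potential impacts of the PP on clinical outcomes". No threshold for suitability is stated.

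Table 1 words question E1 as one about changes in administrative data once the portal has been introduced, not about the effect of using it.

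Elsewhere the article treats patient use as partial. Part B says that actual use is a binary variable for patients. Part C plans interviews with patients who did and who did not use the digital anamnesis (DAC). As a warning about uptake, the Relevance section sets two figures for another product, the insurers' electronic health record, side by side: "62% of the patients with statutory health insurance declared their willingness to use the electronic health record", and then "However, only 0.5% had actually requested it by the end of 2021".

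**The concern.** The premise links an effect of using the portal to a comparison in which users and non-users are averaged together. If only some patients use DAC, the mean over all patients moves by less than the effect in users, and at low uptake by very little. Parts A and C are built on partial uptake, but the reasoning in part E does not mention it.

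Part E is meant to indicate which parameters later projects should use. A flat mean has at least two explanations: the parameter does not respond to portal use, or too few patients used the portal for a response to show. The comparison as described cannot separate them. A responsive parameter could then be set aside for the wrong reason.

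**Working it through.** **Check of method.** Part E states no sample size, effect size, base rate, monthly volume or uptake, so it has no figure to reproduce. The method was checked on the article's other figures. A two-sample t-test with d = 0.2, 80% power and two-sided 5% needs 393.4 per group (the article's 393). A paired t-test needs 198.2 for d = 0.2 (article: 198) and 66.0 for d = 0.35 (article: 66). Only the method and the benchmark d = 0.2 are carried over to part E.

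**Dilution.** Let u be the share of the clinic's patients who use DAC and δ the effect in users. Assume no effect in non-users. Then

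clinic-wide change = u × δ + (1 − u) × 0 = uδ.

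For a mean compared between two time points, n per time point = 2 × (1.960 + 0.842)² / (uδ)², with δ in standard deviations. Relative to full uptake, n is multiplied by 1/u².

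**Benchmark δ = 0.2 in users.** The 62% comes from the article but concerns another product. The other uptakes and the volumes of 1,000 and 3,000 are assumptions.

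| Uptake | 1/u² | n per time point for 80% power | Power, n = 1,000 | Power, n = 3,000 |
|---|---|---|---|---|
| 100% | 1 | 393 | 99% | >99% |
| 62% | 2.6 | 1,021 | 79% | 99.8% |
| 50% | 4 | 1,570 | 61% | 97% |
| 30% | 11.1 | 4,361 | 27% | 64% |
| 10% | 100 | 39,245 | 7% | 12% |

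At 0.5% uptake the multiplier is 40,000 and the required n about 15.7 million.

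**Binary example.** Assumed: 10% base rate, 30% relative reduction in users, 1,000 patients per time point. The clinic-wide rate after introduction is 0.10 × (1 − 0.30u).

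| Uptake | Clinic-wide rate | Power | n per time point for 80% power |
|---|---|---|---|
| 100% | 7.00% | 67% | about 1,350 |
| 62% | 8.14% | 30% | about 3,740 |
| 30% | 9.10% | 10% | about 16,740 |
| 10% | 9.70% | 6% | about 154,880 |

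The multiplier is slightly above 1/u² here because the variance changes with the rate. Not all of the shortfall is dilution: power is only 67% at full uptake, and with an assumed base rate of 2% it is 18% at full uptake.

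**Detectable user effect.** With 1,000 patients per time point and a 10% base rate, the difference detectable with 80% power is about 2.802 × √(2 × 0.1 × 0.9 / 1,000) = 3.8 percentage points. Divided by uptake, this is 3.8 / 0.62 = 6.1 points in users at 62%, and 3.8 / 0.30 = 12.5 points at 30% (from the unrounded 3.76). The last figure exceeds the base rate itself: under these assumptions, even complete elimination of the event in users would not be detected with 80% power.

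**The case against.** The strongest objection is that E1 asks what changes after the portal is introduced, and a mean over all patients at t0, t1 and t2 addresses exactly that. This stands. The choice of population is no error. The mismatch lies between that contrast and the sentence about utilization, together with the suitability reading that follows from it.

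Other objections also limit the point:

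- A reader might infer that responsive parameters will be judged unsuitable. The article does not support this. Part E is exploratory, promises only initial indications and sets no threshold. With d = 0.2 and an assumed 3,000 patients per time point, power is 97% at 50% uptake.
- A reader might infer that part E cannot identify users. The article lists no data fields, and it condenses a fuller protocol that may describe a linkage. Its silence is not evidence.
- A reader might infer that most patients will be non-users. No uptake is forecast for this portal. The 62% and 0.5% concern the electronic health record, and the second is the outcome the project wants to avoid.
- The dilution formula assumes that non-users are unaffected. Physicians must work with the portal, and the Relevance section describes process effects such as fewer telephone contacts, so some spillover is possible and would weaken the dilution.
- Comparing users with non-users would not settle the matter. Hypotheses A4 and A5 predict that use differs by care setting and by frequency of treatment, and both bear directly on readmission and mortality.

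None of this rescues the unconditional premise. An effect of utilization need not be visible in all-patient means when uptake is low.

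**Conclusion.** The point holds in limited form. The clinic-wide comparison is sound for E1, but the premise that improvements from utilization would show in these data is true only in proportion to uptake, and part E attaches no such condition. If non-users are unaffected, the required n rises about 2.6-fold at 62% uptake, 11-fold at 30% and 100-fold at 10%. At low uptake an unchanged mean says little about whether a parameter responds to portal use, and a responsive one could be passed over. At moderate uptake in a high-volume clinic it could still be found. Uptake, base rates, monthly volume and user effects are not in the article, so the power figures are illustrations; the proportionality rests only on the no-spillover assumption. The consequence is confined to what part E may conclude about suitability.

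**What to change.** 1. Report the share of the clinic's patients who used DAC in the t1 month and in the t2 month, on the same denominator as the administrative data.
2. For each parameter, give the confidence interval of the clinic-wide change. Beside it, give the user effect that the comparison could have detected at the observed uptake: detectable difference divided by uptake, stated to assume no effect in non-users.
3. Replace the premise by wording such as: a change in the clinic-wide mean is expected only in proportion to uptake, and an unchanged mean does not show a parameter to be unsuitable.
4. A breakdown by DAC use is optional. If given, label it descriptive and do not use it to judge suitability, because A4 and A5 predict that users differ in care setting and treatment frequency.

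Cost: item 3 is one sentence and needs no new data. Item 2 is a short calculation on data already planned. Item 1 needs a count of DAC users for two months; an aggregate count is enough, without linkage of portal records to cases. Only item 4 needs such linkage, and the article does not say whether it is available.

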## Methods / design

The study follows a longitudinal triple cross-sectional design (pre-post-post). It is based on three consecutive data collection phases, conducted in three clinics of a large academic teaching hospital in Germany. Data will be collected in each of the three clinics 2 months before the implementation (t0), as well as 6 months (t1) and 12 months (t2) after the implementation of the PP. Each of the three clinics has an eight-week period allocated for data collection to achieve the targeted case numbers described below. Quantitative data from surveys of patients (A) and physicians (B), qualitative data from interviews with patients and physicians (C), as well as medical history documentation (D) and administrative data from a participating clinic (E) are used to answer the research questions (Fig. 2). Each of the research questions (A) – (E) will be presented in detail in the following, including detailed case number calculations or sampling strategies.

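### Part E compares one month per time point in one clinic with no comparator, so a change in an administrative parameter is weak evidence that it is suitable for later research

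*Protocol article*

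**What the plan says.** Part E of Methods / design uses "hospital data collected for administrative purposes from one participating clinic". The window is fixed: "The data consist of administrative data for all outpatient and inpatient patients within a month at the three measurement points (t0; t1; t2". The opening paragraph of Methods / design sets the points at "2 months before the implementation (t0), as well as 6 months (t1) and 12 months (t2) after the implementation of the PP".

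The outcomes are given as examples, "such as the 30-day readmission rate, inpatient mortality, or 30-day mortality are analyzed", and the analysis uses "descriptive and inferential statistics to compare the means of the examined parameters regarding potential differences at the three measurement points". No comparison clinic, longer series or same-month reference is described.

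The premise is that "If the utilization of PP leads to improvements in clinical outcomes, these improvements would be reflected in the administrative and clinical management data". The ambition is modest: "an exploratory analytical approach is applied to the hospital data collected for administrative purposes", and "The results provide initial indications of whether the parameters investigated here are suitable for assessing potential impacts of the PP". Table 1 also lists E1 as an exploratory question.

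**The concern.** E1 asks what changes after the portal is introduced, and the answer is meant to guide the choice of outcomes for future studies. With one pre-implementation month and two later ones, each period is a single draw. Whatever else differs between those months (season, case-mix, trend, ordinary fluctuation) is completely aliased with portal exposure.

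This is a property of the data window, which the article fixes. It is not an analysis detail that a fuller document could supply, because no model fitted to these three months alone can separate the portal from the calendar.

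At stake is part E's one task. A parameter may look responsive because two months happened to differ, or look inert because one month held too few events.

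**Working it through.** **Inputs from the article.** One month per point; points at -2, +6 and +12 months; one clinic; comparison of means with inferential statistics. Part E states no sample size, event rate or effect size, so there is no figure to reproduce.

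**1. Calendar distance.** Distance = min(gap mod 12, 12 - gap mod 12).

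| Contrast | Gap (months) | Calendar months apart |
|---|---|---|
| t0 vs t1 | 6 - (-2) = 8 | 4 |
| t1 vs t2 | 12 - 6 = 6 | 6 |
| t0 vs t2 | 12 - (-2) = 14 | 2 |

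These are nominal distances. Each clinic has an eight-week collection period, and part E does not say where in it the month lies.

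**2. Month-to-month variation (assumed ICC).** Let ICC be the share of outcome variance lying between months. With n patients per month and unit variance, the true variance of a two-month difference is 2(1 - ICC)/n + 2 ICC, while a patient-level test uses 2/n. The ratio is 1 + (n - 1) ICC, so the actual type I error is 2[1 - Φ(1.96/√(1 + (n - 1) ICC))].

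| ICC | n = 200 | n = 500 | n = 1000 |
|---|---|---|---|
| 0.001 | 7% | 11% | 17% |
| 0.005 | 17% | 29% | 42% |
| 0.01 | 26% | 42% | 55% |

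Example: n = 500 and ICC = 0.001 give √1.499 = 1.224, then 1.96/1.224 = 1.60 and an error of 11%. More patients per month make this worse; only more months help.

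**3. Season alone (assumed swing, no portal effect).** If a 10% rate is 30% higher in relative terms in one month (10% versus 13%), a two-sided 5% test is significant in 32% of comparisons at n = 500 and 56% at n = 1000.

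**4. Precision (assumed rates and volumes).** The 95% half-width of a two-month difference is 1.96 √(2p(1 - p)/n). Power is for a two-sided 5% test of two proportions.

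| Rate p | n per month | Half-width (points) | Power, halving | Power, 20% relative reduction |
|---|---|---|---|---|
| 2% | 200 | ±2.7 | 13% | 5% |
| 2% | 500 | ±1.7 | 26% | 7% |
| 2% | 1000 | ±1.2 | 45% | 10% |
| 10% | 200 | ±5.9 | 48% | 10% |
| 10% | 500 | ±3.7 | 85% | 20% |
| 10% | 1000 | ±2.6 | 99% | 35% |

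A 2% outcome is imprecise throughout this range. A 10% outcome is adequate for a halving from about 500 per month, but not for a 20% reduction.

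**5. What more pre-implementation months buy.** With 24 equal pre-months, the sampling SE of the pre-period mean falls by √24 ≈ 4.9. Against a single post month, the SE of the difference falls only to √((1 + 1/24)/2) = 0.72 of its value, about 28%. The series should therefore also run through t2. The further gain is that month-level variation and season become estimable.

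**The case against.** The strongest reply is that part E is exploratory. It promises initial indications for further research, opens by calling it unclear how suitable these data are, and claims no portal effect. This stands, and it lowers the severity. It does not remove the point, because the inferential comparison is still planned and an initial indication from three single months is weak even on its own terms.

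A reader might infer more than the article supports:

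- **That season confounds every contrast.** It does not do so equally. t0 and t2 are nominally two calendar months apart and so roughly season-matched; trend and month-level variation remain there.
- **That suitable parameters cannot be identified at all.** That holds exploratory work to a confirmatory standard.
- **That parameters will be kept or dropped on significance.** No such rule is stated.
- **That the outcomes are too rare to study.** The named outcomes are only examples, volumes are not given, and all outpatients and inpatients of the clinic are covered. At 10% and 500 per month, a halving would have about 85% power.

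Model choice and case-mix adjustment may properly be left to an analysis plan that is not shown, so their absence is not held against the article.

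**Conclusion.** The point holds in limited form. One month per period in one clinic, without a comparator, confounds month-to-month variation and secular trend with the portal in all three contrasts, and season materially in two of them. A change, or no change, in a parameter is therefore weak evidence of its suitability.

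The aliasing follows from the stated design and needs no assumption. Its size does: the error rates of 11% to 42% at 500 per month rest on an assumed ICC of 0.001 to 0.01, and the seasonal and precision figures on assumed swings, rates and volumes. Low-rate outcomes such as mortality may be imprecise in a single month; whether they are depends on volumes that the article does not give.

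Severity is low because part E is exploratory, but the correction is cheap and should be made before the data are requested.

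**What to change.** **Preferred.** Export the same routine parameters as a monthly series from before implementation through t2 (for instance 24 pre-months), with 30 days of follow-up after the last month for the 30-day outcomes. For event rates, use a segmented or calendar-month-adjusted binomial or Poisson model that allows for variation between months. Report estimates with confidence intervals and judge suitability on those.

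**Minimum.** Add the calendar months of t1 and t2 from before implementation. The match for t1 is 6 - 12 = -6 months. For t2, 12 - 12 = 0 is implementation itself, so the match is 12 - 24 = -12 months. This addresses season, but not trend or single-month noise.

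**If only the three months are available.** Present the comparison as descriptive, drop the significance tests, and state that differences cannot be attributed to the portal.

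**Cost.** A larger export of data collected routinely for administration, data-access paperwork and some analyst time. No additional patient contact is needed. Whether earlier months can be retrieved should be confirmed with the clinic, as the article does not say.
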